### *Specific aims (secondary)*

3. Check conclusions from the primary time series analysis using an SMR-based approach that compares observed and expected mortality for given week of the year.
4. Conduct an exploratory cohort analysis using individual-level data to investigate how excess mortality varies by characteristics including specified combinations of comorbidities.

### *Rationale:*

Excess deaths by week from any cause could provide the most objective and comparable way of assessing the net impact of the pandemic as it progresses, and avoids the significant problems associated with attributing individual deaths to COVID-19. Use of alternative techniques in secondary and exploratory analyses will allow us to estimate the robustness of our model and potentially extend our analyses to less common comorbidities and multimorbidity groups.

## F. Study Background

Accurate and consistent estimation of key population parameters is required to inform national and global strategies to mitigate and suppress progression of the coronavirus disease 2019 (COVID-19) pandemic. Essential parameters include mortality due to COVID-19. However, variation in testing and recording of cause of deaths in national death registers between countries, over time and by underlying health conditions makes this challenging. Excess mortality over time may therefore be a more objective and comparable way of assessing the scale of the pandemic and formulating lessons to be learned. It is constructed by comparing the deaths over time in 2020 to the number expected based on the experience of previous non-pandemic years. Crucially this method has as the outcome all-cause mortality, sidestepping the problems associated with attribution of cause of death to COVID-19.

It is possible to estimate excess mortality by age, sex and geographic region using national death registration data although there is a delay in publishing these. These methods have been used to measure excess deaths in previous influenza seasons and are being used for the COVID-19 pandemic.

Current methods using death registration data alone do not allow stratified estimation of excess deaths for groups of people with clinical risk factors for COVID-19. CPRD uniquely includes timely data on deaths alongside extensive clinical and demographic data, backed up by periodic linkages to national mortality data. This study will exploit this important combination of demographic/clinical and death data to examine how pre-existing illnesses (e.g. respiratory disease, heart disease, diabetes) and risk factors such as BMI and smoking are associated with excess mortality risk during the course of the pandemic. The study will provide key information to inform clinical guidance, resource planning and policies for protecting the most vulnerable.

[figure not shown]

### G. Study Type

Descriptive

### H. Study Design

For our primary analysis, we will use time series methods modelling weekly counts of deaths through regression models that incorporate seasonal parameters and annual trends and use interaction terms with pandemic indicators to estimate excess mortality after the pandemic and effect modification by patient characteristics. To check the robustness of the results, we will use SMR methods which split the time-series data into pre-COVID-19 and COVID-19 periods and use weekly aggregated data from the former to predict expected mortality rates in the latter.

In exploratory analyses, we will develop individual cohort designs which may allow us to estimate more granular patient characteristics (e.g rare comorbidities and multimorbidity groups). Differences between models will be examined and reported on.

### I. Feasibility counts

Counts based on April 2020 builds

|                                                                      | CPRD GOLD                               | CPRD Aurum            |
|----------------------------------------------------------------------|-----------------------------------------|-----------------------|
| Alive and registered with up to standard* practice on 1 January 2020 | 3 152 150                               | 11 090 586            |
| UK countries represented                                             | All                                     | England and N Ireland |
| English regions represented                                          | All except North East and East Midlands | All                   |
| Median (IQR) weekly deaths in 2019                                   | 560 (537-620)                           | 1657 (1549-1845)      |
| January 2019 deaths                                                  | 3066                                    | 8563                  |
| January 2020 deaths                                                  | 2747                                    | 8318                  |
| February 2020 deaths                                                 | 2115                                    | 6613                  |

\*Up to standard date only available in CPRD GOLD

[figure not shown]

#### J. Sample size considerations

We will use all available data in CPRD GOLD and CPRD Aurum to maximise regional coverage and the number and combination of comorbidities that we can study whilst modelling changes on a weekly basis. Data extraction will be minimised by using the CPRD GOLD Define and Refine tools to ascertain covariates of interest only, rather than extracting full clinical data (as discussed with [name] and [name]).

Methods for computing sample size and power are not well developed for time series analysis, so we took an empirical approach by combining recent CPRD GOLD denominator data with a simulated pandemic starting in week 9 of the final year which doubles death rates and affects patients with a given comorbidity (simulated to have similar prevalence to cancer) twice as badly. Using the time series approach, the IRR (95% CI) for the pandemic was 1.89 (1.74-2.07) and the comorbidity interaction (1.97, 1.85-2.08). The confidence intervals included the true values (2.0 and 2.0) with adequate precision. We therefore expect the coverage to be good with this study size, even when estimating interaction terms. 8% of cells had zero denominators in the weekly time series dataset created from these simulated data, necessitating some collapsing of strata, and this would rise further if stratifying by >1 comorbidity, hence the need for maximum data (using both GOLD and Aurum) to enable us to explore joint associations of combinations of covariates, using mutually adjusted models.

We will use the July 2020 build for the initial primary care only analyses because these data are the most timely and updated monthly. Our study period will end on 30 April 2020 as there appears to be a two-month delay in registering deaths in primary care data. Analyses will be updated monthly.

#### K. Planned use of linked data (if applicable):

Additional analyses will be completed when set 19 of the linkage data is released, assuming that ONS linked data coverage will then include the pandemic period. We request access to linked ONS mortality data so that analyses can be repeated using ONS certified death as the outcome and linked HES admitted patient care data to improve ascertainment of ethnicity and comorbidities for stratification in later analyses.

Linked practice level Carstairs quintiles are requested to allow stratification by area-based deprivation in the initial analyses using primary care data only. We also request urban rural data as COVID-19 infections and mortality will be affected by deprivation, population density and distance from hospital. **Patient level Carstairs quintiles are requested for the linked analysis.**

Risk of identification of practice or patient location will be mitigated by restricting users who have access to the raw CPRD and linked data to [name] and [name] who understand the increased risk of identification with these data and have completed mandatory data protection training at LSHTM. This will be implemented by password protecting folders where data are stored in accordance with LSHTM IT policy. Patient and practice identifiers will be pseudonymised in datasets released to other investigators.

Analyses using linked data will be restricted to English practices and patients who are eligible for linkage, and to the time periods of linked data coverage.

**This study will use demographic/clinical and death data available in CPRD primary care and linked data sources to examine how pre-existing illnesses (e.g. respiratory disease, heart disease, diabetes) and risk factors such as BMI and smoking are associated with excess mortality risk during the course of the COVID-19 pandemic in the UK. The findings will provide key information to inform clinical guidance, resource planning and policies for protecting the most vulnerable people in the UK, including in England and Wales, during the pandemic.**

[figure not shown]

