##### **1) Time series and SMR approaches**

The study population will be the adult population of all practices with continuous follow-up from 1st March 2014 and with last data collection dates no more than 2 months before the date of the most recent CPRD build ("time-series cohort").

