### 1) Primary analysis - time series approach

We will derive weekly counts of numbers of deaths in contributing practices (see section L “Study Population”) from the start of the study period to the end of the study period. Population denominator sizes (number under active follow-up) will also be extracted. We will extract these counts overall, and stratified by age, sex, region and other factors (see section N “Covariates”). Where these factors are time-varying, counts will reflect changes over time.

We will fit generalised linear models with a negative binomial error structure to model the counts of deaths, taking account of variable denominator sizes [approach we took in Matthews et al media and statins paper to deal with variable denominators, BMJ2016]. The model will initially include the outcome (mortality), exposure (2020 pandemic period vs pre-pandemic), age, sex, interactions between the exposure and age and sex, Fourier terms (a harmonic function of calendar week) to capture seasonality, a continuous function of calendar year (linear, or higher order polynomial if evidence of non-linearity) to capture any underlying trends, and if relevant dummy indicators to capture extreme flu seasons. When investigating excess mortality within subgroups, further exposure covariate stratification factors will be added individually, and in combinations where there is sufficient information. Interactions between the exposure and stratification factors will provide estimates of the relative effect of the pandemic in strata.

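### Intervals for pandemic interactions with practice-level deprivation and urban-rural class leave out practice-to-practice variation in the pandemic effect, so their coverage is not assured

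*Protocol*

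**What the plan says.** The study population for the time series is "the adult population of all practices with continuous follow-up" from March 2014 (Section L.1).

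For deprivation, Section K states: "Linked practice level Carstairs quintiles are requested to allow stratification by area-based deprivation in the initial analyses using primary care data only". The patient-level measure comes later: "Patient level Carstairs quintiles are requested for the linked analysis". On urban-rural class the same section says "We also request urban rural data as COVID-19 infections and mortality will be affected by deprivation, population density and distance from hospital", and the area-level table under item 13 has this ticked in the practice column, not the patient column. In the initial analyses, therefore, every patient of a practice falls in the same stratum of either factor. Neither factor is in the covariate list of Section N. Section K nevertheless states the deprivation stratification outright; for urban-rural class the use has to be inferred from the request.

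Section O.1 fixes the aggregation, "We will derive weekly counts of numbers of deaths in contributing practices", and the model: "We will fit generalised linear models with a negative binomial error structure to model the counts of deaths, taking account of variable denominator sizes". The result of interest is named there too: "Interactions between the exposure and stratification factors will provide estimates of the relative effect of the pandemic in strata". No practice term or practice-based variance is mentioned.

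Section J concludes from one simulation that coverage should be good, interaction terms included. The factor simulated was a patient-level comorbidity.

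**The concern.** Suppose a practice is hit harder than average and stays so through the pandemic weeks. After pooling, its extra deaths raise the pandemic mean of the stratum to which the whole practice belongs. The pandemic-by-stratum coefficient absorbs that shift. It does not appear as scatter of weekly cells around the fit, so the negative binomial dispersion parameter cannot pick it up, and practice identity is no longer in the data. Chance differences in which practices fall in a quintile could then be read as differences in pandemic effect, with an interval that does not reflect them.

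The simulation in Section J does not settle this, because it says nothing about a factor that varies only between practices. The SMR check in Section O.2 does not either: it reuses the same stratified counts and takes its intervals from a saturated Poisson model, so agreement between the two approaches would not reveal the problem. Section S intends early release to inform policy, and the practice-level strata belong to those early analyses.

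**Working it through.** **The protocol's own figures.** Section J reports a pandemic IRR of 1.89 (1.74-2.07) and a comorbidity interaction of 1.97 (1.85-2.08). They cannot be reproduced, because the underlying denominators are not given. They are internally consistent: SE(log) = ln(U/L)/(2 × 1.96) gives 0.044 and 0.030, with geometric midpoints 1.898 and 1.962. There is no corresponding figure for a practice-level factor.

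**Inputs.**
- Weekly deaths, from the medians in Section I: 560 + 1,657 = 2,217. This ignores overlap between the two databases. Only deaths per practice enter the formula below.
- Pandemic window, Sections J and N: 1 March to 30 April 2020, 61 days = 8.71 weeks.
- Assumed, not in the protocol: K = 1,000 to 1,800 practices, mean pandemic rate ratio 1.5, and τ, the between-practice SD of the log pandemic rate ratio, from 0.1 to 0.4.

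**Closed form, flat effect.** Let a stratum hold n practices with m pandemic-period deaths each. Ignoring the small contribution of the long baseline, the model variance of the stratum's log pandemic rate is 1/(nm). The true variance is 1/(nm) + τ²/n. Hence

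SE ratio (true/model) = √(1 + mτ²), with m = 2,217 × 8.71 × 1.5 / K.

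The numerator of m is about 28,980.

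| K | m | τ = 0.1 | τ = 0.2 | τ = 0.3 | τ = 0.4 |
|---|---|---|---|---|---|
| 1,000 | 29.0 | 1.14 | 1.47 | 1.90 | 2.37 |
| 1,400 | 20.7 | 1.10 | 1.35 | 1.69 | 2.08 |
| 1,800 | 16.1 | 1.08 | 1.28 | 1.56 | 1.89 |

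For example, with K = 1,400 and τ = 0.2: √(1 + 20.7 × 0.04) = √1.83 = 1.35.

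**Simulation of the pooled model.** Deaths by week, age, sex and quintile were fitted with a negative binomial GLM with Fourier terms, trend and pandemic interactions, for 1,400 practices of unequal size. The entries are the ratio of empirical to model SE for quintile 5 against 1, with coverage of the 95% interval in brackets.

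| Pandemic effect | τ = 0 | 0.1 | 0.2 | 0.3 | 0.4 |
|---|---|---|---|---|---|
| Flat, no weekly noise | 0.99 (98%) | 1.12 (92%) | 1.39 (83%) | 1.93 (67%) | 2.34 (60%) |
| Flat, common weekly noise (SD 0.06) | 0.88 (97%) | 1.17 (92%) | 1.35 (88%) | 1.72 (72%) | 1.82 (73%) |
| Rising and falling, single indicator, same noise | 0.80 (100%) | 0.83 (100%) | 0.91 (97%) | 1.27 (88%) | 1.77 (70%) |

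With 60 replicates per setting, the ratios carry a Monte Carlo error of about 9%. In the third row the weekly rate ratios run from 1 to 2.2 with mean 1.5. A single indicator misfits that wave, and the misfit inflates the dispersion (about 0.010, against 0.003 in the second row and 0.0001 in the first) and with it the model SE. The wave is common to all quintiles and largely cancels in the comparison between them, so the model SE is too large until τ is big enough to outweigh it.

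**The case against.** **The intervals might not be too narrow at all.** This stands in part. A reader might infer that the planned intervals are certainly too narrow. The protocol does not support that: τ and the number of practices are not given, and under a wave-shaped effect with τ up to 0.2 the intervals were conservative. A further direct negative binomial fit with coarse cells and independent overdispersion (dispersion 0.02, 200 runs) gave a false-positive rate of 6.5% at τ = 0.2 against 7.0% at τ = 0, so no detectable effect there, and 11.5% at τ = 0.3. What remains is that any adequate coverage at small τ would come from two errors offsetting each other.

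**The variance estimator belongs in a statistical analysis plan.** Section O.1 does not exclude a robust variance, and Section K shows that pseudonymised practice identifiers are available. But the protocol does fix the pooling step, and Section J makes a coverage statement without excepting practice-level factors.

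**The scope is peripheral.** This is largely right. The linked analysis moves to patient-level Carstairs, and Section N does not list these factors. Stable differences between practices largely cancel, because the same practices supply their own baseline from 2014; only practice-by-pandemic variation counts. Region, which is a listed stratifier, could absorb part of it.

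**Other factors.** A reader might extend the point to care-home residency and household size. Both can vary within a practice, so a practice-wide shock largely cancels. Clustering within homes is a different mechanism that was not examined here.

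**Monthly updates.** A reader might also infer that the problem must grow as deaths accrue. That would require τ to persist, which nothing in the protocol shows.

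**Conclusion.** The concern holds in limited form. In the initial analyses, the intervals for pandemic interactions with practice-level Carstairs and urban-rural class leave out practice-to-practice variation in the pandemic effect, and their coverage is not assured.

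Under a flat effect, a mean rate ratio of 1.5 and 1,000 to 1,800 practices, the true SE is about 1.1 times the model SE at τ = 0.1, 1.3 to 1.5 times at 0.2 and 1.6 to 1.9 times at 0.3. Under a rising-and-falling wave with one indicator, the simulated intervals are too wide for τ up to 0.2 and too narrow from about 0.3. All of this rests on assumed values of τ and the number of practices.

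The point estimates are not in question, nor are the interactions with patient-level comorbidities or the later patient-level deprivation analysis. It is worth acting on because the remedy is cheap and estimates the right variance whichever way the model-based one errs.

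**What to change.** In Section O.1, state that for strata defined on practices (practice-level Carstairs, urban-rural class) the 95% intervals for the pandemic interaction will come from practice-clustered inference. Either of two methods will do:
- resample whole practices, rebuild the weekly counts and refit the same negative binomial model; or
- keep the pseudonymised practice identifier in the count data and use practice-cluster-robust standard errors.

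Model and point estimates stay as planned.

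In Section J, limit the expectation of good coverage to patient-level factors such as the comorbidity that was simulated.

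The cost is a sentence in each section, retention of the practice identifier in the count extraction, computing time and possibly wider intervals. Correlation between neighbouring practices that share a local epidemic is not removed by this change and should be acknowledged as a remaining limitation.

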#### **L. Definition of the Study population**

Data from practices that have contributed to both CPRD GOLD and CPRD Aurum will be removed from the CPRD Aurum cohort to maximise the power of analyses that can only be completed in CPRD GOLD (i.e. stratification by number of people in household).

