##### **2) Cohort approach**

The population under investigation will be the adult population contributing CPRD follow-up at any time after 1st March 2014.

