## O. Data/ Statistical Analysis

To ensure our conclusions are robust, several approaches will be taken (with different strengths and limitations). We would expect the overall patterns and conclusions of the analyses to be similar. Any discrepancies in the patterns or results will be investigated and reported. In each case we will use data up to two months before the CPRD build date (i.e. data to end April 2020, from the build released in early July 2020) and analyses will be updated monthly.

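### Section L removes the Aurum copy of every dual-database practice, even where its GOLD copy fails the recency rule, so the time-series and SMR analyses can lose an eligible practice altogether

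*Protocol*

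**What the plan says.** Section L of the protocol opens with an overlap rule for all analyses: "Data from practices that have contributed to both CPRD GOLD and CPRD Aurum will be removed from the CPRD Aurum cohort". The reason given is "to maximise the power of analyses that can only be completed in CPRD GOLD", with stratification by household size as the case in point. Section N adds care home residency as a second covariate available only in GOLD.

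Section L.1 then defines the time-series and SMR population. Practices need continuous follow-up from 1 March 2014, and they must be practices "with last data collection dates no more than 2 months before the date of the most recent CPRD build". Section O ties this to a specific release: "data to end April 2020, from the build released in early July 2020", with monthly updates afterwards. Section L.2 defines the cohort population as adults with any CPRD follow-up after 1 March 2014 and sets no recency condition.

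Section J gives the aim on data volume: "We will use all available data in CPRD GOLD and CPRD Aurum to maximise regional coverage". Section I lists the English regions in GOLD as "All except North East and East Midlands" and those in Aurum as all. The protocol does not say how many practices have contributed to both databases, nor in which order the overlap and eligibility rules are applied. The closing section on changes to the approved protocol does not mention either rule.

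**The concern.** The overlap rule is triggered by contribution to both databases at any time, whereas the recency rule looks at current contribution. The two therefore work against each other for a practice that has left GOLD and continues in Aurum. The GOLD copy is too old to enter the time-series cohort, and the Aurum copy is removed because the GOLD copy once existed.

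For such a practice the overlap rule does not serve its own purpose. There is no double counting to prevent in the time-series cohort, and the practice adds no power to the household or care home analyses because it is not in the GOLD cohort. What is at stake is usable deaths and person-time in the primary analysis. Section J says that maximum data from both databases are needed, because 8% of cells had zero denominators in its simulated weekly dataset and further stratification would raise that share.

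**Working it through.** **Step 1: recency cut-off.** The build is released in early July 2020 (Section O). Two months earlier is early May 2020, taken here as 1 May 2020. The cut-off moves forward with each monthly build.

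**Step 2: the rules as worded, applied to six practice histories.** Eligibility is judged within each database, and continuity from 1 March 2014 is assumed wherever the feed is current.

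| Practice history | GOLD | Aurum, as written | Aurum, if overlap is removed after eligibility |
|---|---|---|---|
| Current in GOLD only | kept | none | none |
| Current in Aurum only | none | kept | kept |
| Current in both | kept | removed | removed |
| Left GOLD in 2017, current in Aurum | fails recency | removed | kept |
| Left GOLD in April 2020, current in Aurum | fails recency | removed | kept |
| Left GOLD in late May 2020, current in Aurum | kept for this build | removed | removed for this build |

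The fourth and fifth histories are lost from both databases. The sixth is safe for the July build, but is lost at a later update once its last GOLD date is more than two months old. Removing overlap after eligibility keeps every practice exactly once.

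**Step 3: the cohort approach.** With no recency rule, a practice that left GOLD keeps its GOLD time up to the date it left. Its Aurum time is discarded, including the pandemic period if it left before March 2020.

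**Step 4: size.** The protocol states no figure for the overlap, so there is none to reproduce. The inputs are the Section I counts: 11 090 586 people registered in Aurum on 1 January 2020, and median weekly deaths in 2019 of 560 (GOLD) and 1657 (Aurum), together 560 + 1657 = 2217. Let f be the assumed share of Aurum that sits in affected practices. Then people lost = 11 090 586 × f; weekly deaths lost = 1657 × f; share of deaths lost, x = 1657f / 2217; standard error multiplier ≈ 1/√(1 − x), taking the standard error as inversely proportional to the square root of deaths.

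| f (assumed) | People | Weekly deaths | x | Standard error multiplier |
|---|---|---|---|---|
| 1% | 110 906 | 17 | 0.7% | 1.00 |
| 5% | 554 529 | 83 | 3.7% | 1.02 |
| 10% | 1 109 059 | 166 | 7.5% | 1.04 |
| 20% | 2 218 117 | 331 | 14.9% | 1.08 |

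Section I does not say whether practices in both databases are counted twice. If they are, 2217 is somewhat too large and x somewhat too small.

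**The case against.** The strongest reply is that Section L states no sequence and does state a purpose. Read by that purpose, the overlap rule covers only practices that would otherwise sit in both analysis cohorts, and an analyst who filters first and removes overlap afterwards loses nothing. That may well be the intention, but the wording turns on having contributed to both databases and makes no exception for a lapsed GOLD feed. If recency were instead judged per practice across the two databases, the practice would stay in GOLD with data that stop before or during the pandemic, which is also a defect.

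Several limits do stand:

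- **Affected practices.** No document shows that any practice left GOLD and is current in Aurum, or that its Aurum record reaches back to 1 March 2014. Without that continuity, Section L.1 excludes it anyway.
- **Regions.** A reader might infer from Section I that the North East and East Midlands lose coverage. The documents do not show that former GOLD practices exist there, and Aurum practices that never fed GOLD are untouched.
- **Bias.** A reader might infer that loss by database history biases the results. The primary contrast is pandemic against pre-pandemic in practices followed throughout, so an excluded practice leaves both periods, and nothing in the documents links database history to excess mortality.
- **Precision.** Even at the assumed 20%, 2217 − 331 = 1886 weekly deaths remain, about 3.4 times GOLD's 560. Section J judged precision adequate in a simulation on GOLD denominators alone, although it wanted more data for joint strata.
- **Later restrictions.** The final section reports a restriction to people aged 40 and over, and conditions left unreported, because of low numbers of deaths. Nothing there ties this to the overlap rule.

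**Conclusion.** The concern holds for the time-series and SMR analyses. As worded, Section L loses a practice from both databases when its GOLD feed has lapsed beyond the recency window and its Aurum record is otherwise eligible. It does not hold for every dual practice: those current in both databases, or with a last GOLD collection inside the two-month window, are kept once in GOLD as intended. In the cohort approach the practice is not deleted, but its Aurum follow-up is. The final section says that the cohort analysis was not attempted, so the main practical consequence is for the primary time series.

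The demonstrable cost is precision and coverage. Its size rests wholly on an assumed share of Aurum and could be negligible (0.7% of weekly deaths at 1%) or moderate (about 15% at 20%). The conclusion rests on reading recency within each database and the overlap wording literally. Section L should be corrected because the stated rule works against its own purpose and the correction is cheap.

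**What to change.** Reword Section L so that, for the time-series and SMR approaches, the continuity and recency rules are applied within each database first. The Aurum copy is then removed only if the same practice is eligible in GOLD; otherwise the Aurum copy is kept. Report the number of practices at each step, including how many have contributed to both databases, which would replace the assumed range above with a fact.

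For the cohort approach, which has no recency rule to order, state which single source is kept for a dual practice, chosen so that pandemic-period follow-up is not lost.

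The cost is a sentence or two in Section L and a reordered filter. It uses the practice matching that the overlap rule already needs, and double counting is still prevented. There is a small downside: a practice whose GOLD feed lapses may switch from its GOLD to its Aurum copy between monthly updates, and would then lack the household and care home covariates. Any such switches should be reported with the update in which they occur.
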